Against this background, we designed and developed treatment protocols, which consist mainly of either rescripting of, or exposure to, the nightmare content. Such stripped-down versions of exposure and rescripting for nightmares allow us to investigate the therapeutic efficacy of these treatments without any (possibly distorting) influence of nonspecific treatment components. While knowledge about the efficacy of pure rescripting and exposure for nightmares might be valuable to appraise the importance of different processes underlying psychological treatments for chronic nightmares, stripped-down treatment protocols have another significant advantage. Namely, using stripped-down versions of IE and IR in the treatment of nightmares may help to identify their mediating mechanisms. Thus, in order to (1) identify mediators of the treatment effect that (uniquely) contribute to the efficacy of IE versus IR, we aim to (2) establish the efficacy of each of these stripped-down treatments when compared to a waiting-list control group. In line with previous research, it is hypothesized that both treatments will effectively reduce nightmare symptoms [10, 11]. Potential differences between IR and IE will be explored. With regard to the mechanisms of change, we assume that both treatments target different key processes. This assumption is mainly based on current theories about the working mechanisms of IR and IE for nightmares. Specifically, we hypothesize that nightmare distress and tolerability of emotions elicited by nightmares might be critical mediating variables of the treatment effect of IE. In contrast, nightmare valence and mastery of the nightmare content might be particularly important mediators of the treatment effect in IR. However, given the limited empirical knowledge about the underlying mechanisms of nightmare treatments (especially IR), we cannot exclude the possibility that a number of the selected mediators might play a critical role in both treatments (e.g., predictability and controllability of emotions elicited by nightmares, and sleep quality), rather than being exclusive to either IR or IE. Therefore, we will further explore if the proposed variables play a unique role in either rescripting-based or exposure-based nightmare treatments, or whether they could be relevant mediators of therapeutic change in both therapies.

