### Sample size

The proposed study was powered to detect differences between the treatments (i.e., IR and IE) compared to the WL condition. A power calculation (two-sided, power = 80 %, alpha = 0.05; G*Power 3.1) with a medium to large effect size for individual nightmare therapy (*d* = .74; [10]) showed that 30 participants in each condition would suffice to detect a statistically significant difference between each of the two treatment conditions and the WL condition. Thus, a total of 90 participants will be included in the proposed study and potential dropouts will be replaced.

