#### Mediation

Mediators of the treatment effects for IR and IE will be analyzed according to the following steps: (1) mediator variables, which show a change during the course of treatment, will be included in the statistical model. For this purpose, the means across and within subjects over time will be inspected for all eight proposed mediators. In order to reduce the number of relevant mediator variables, we will inspect the association between the proposed mediators over time. A composite score will be calculated for those mediator variables that are highly associated with each other if their theoretical conceptualization allows for it. (2) In a series of separate mixed regression analyses, statistically relevant mediator variables will be selected from the remaining mediator variables. To that end, the effect of each mediator on treatment outcome will be explored regardless of treatment condition. Each mediator score (measured the day after pre-assessment and after all treatment sessions) will be used to predict treatment outcome at the following assessment (i.e., 6 days/nights later). (3) Only those mediator variables that have an effect on treatment outcome will subsequently be added to a final mixed regression model, taking treatment condition into account. Fixed factors in the model will, therefore, include: treatment condition (IE and IR), relevant mediators, time, and their interaction, as well as any relevant covariate that might reduce error. The covariance structure of the repeated part will be determined by empirically assessing the best fitting structure. If possible, random parts on the participant level will be added. Note that if a mediator represents a working mechanism, the strength of the association between mediator and effect (i.e., outcome) should be similar in all conditions [71]. Therefore, to investigate whether there is a difference between the working mechanisms of IR and IE, we will test whether the mean change for each mediator differs between treatment conditions (i.e., the larger the change, the more the treatment affects the mediator, indicating that the working mechanism is strongly triggered by the treatment). Also, we will inspect the percentage of variance of the clinical effect explained by each mediator, and whether treatments differ in the percentage of variance explained by a specific mediator. (4) In a last step, all previously determined relevant mediator variables will subsequently be tested with separate mediation analyses for IE and IR (with WL as a reference group). Difference scores of mediator assessments will be used to predict post-assessment outcomes. Pre-treatment levels of the dependent and mediator variables will be added to the model as covariates (see also [64]). Both single and multiple mediation analyses will be performed. Mediation will be tested by evaluating the 95 % confidence interval of the indirect effect (i.e., the effect of the intervention (IE or IR) on treatment outcome through a specific mediator). For these analyses, we will use bootstrapping [72, 73], a nonparametrical procedure that produces an estimate of the sample distribution based on several resamples. For the proposed analyses, a minimum of *n* = 5000 bootstrap resamples will be generated. To the best of our knowledge, bootstrap mediation is currently not available for mixed regression. Unless such a technique is available by the time of the analyses, we will execute the bootstrap mediation test on the subsample with complete data, as well as on the complete sample with missing values imputed, to check for consistency of results. A multiple imputation procedure based on 20 datasets will be used to replace missing values.

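### Step 4 of the mediation plan tests IE and IR separately against waiting list, gives no interval for the difference between the two indirect effects, and does not say whether step 3 or step 4 decides uniqueness

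*Protocol article*

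**What the plan says.** Under Trial objectives, the first aim is to "identify mediators of the treatment effect that (uniquely) contribute to the efficacy of IE versus IR". The same section predicts that distress and tolerability matter for IE, and valence and mastery for IR. It then frames the broader question as exploratory: "we will further explore if the proposed variables play a unique role in either rescripting-based or exposure-based nightmare treatments".

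The Mediation section has two steps that bear on this aim.

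- **Step 3.** To examine whether the working mechanisms differ, "we will test whether the mean change for each mediator differs between treatment conditions". The reason given is that the mediator-outcome association should be similar in every condition if the mediator is a true mechanism. Differences in variance explained are also to be inspected.
- **Step 4.** The retained mediators are "tested with separate mediation analyses for IE and IR (with WL as a reference group"). Each indirect effect is judged by its own 95% bootstrap interval from at least 5000 resamples. No interval for the IE-minus-IR difference is described.

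The text does not say how to read a mediator that passes step 4 for one therapy and fails it for the other.

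**The concern.** One interval that excludes zero and another that does not are no evidence that the two effects differ. Step 4 produces exactly such a pair of verdicts for each mediator, in a trial whose first aim is about uniqueness.

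Step 3 supplies a between-treatment test, but only on the treatment-to-mediator path. It equals a comparison of indirect effects when the mediator-to-outcome path is common to the arms. Step 4 does not use that premise: it estimates the path once in IE plus WL and once in IR plus WL. The two steps therefore rest on different assumptions and can point in different directions, with no stated order of precedence.

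At stake is how the planned mechanisms paper reads a discordant pair. The primary efficacy analysis is not affected.

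**Working it through.** **1. The plan's own figure.** The Sample size section gives "two-sided, power = 80 %, alpha = 0.05; G*Power 3.1", a "medium to large effect size for individual nightmare therapy (*d* = .74; [10"]), and concludes that "30 participants in each condition would suffice to detect a statistically significant difference between each of the two treatment conditions and the WL condition". For a two-sample t-test with n = 30 per arm, the noncentrality is 0.74 × √(30/2) = 2.87 on 58 degrees of freedom, which gives 80.5% power. With n = 29 the power is 79.1%. The figure of 30 is reproduced. It concerns each therapy against WL on the clinical outcome, not mediation.

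**2. What each step tests.** Let a be the treatment-to-mediator effect against WL and b the mediator-to-outcome path.

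- Step 4 tests a_IE × b_IE = 0 and, separately, a_IR × b_IR = 0, with b_IE from IE + WL (60 people) and b_IR from IR + WL (60 people).
- The contrast for uniqueness is a_IE × b_IE − a_IR × b_IR. If b is common, this becomes b × (a_IE − a_IR). With b not zero, it is zero exactly when the mediator changes are equal, which is step 3's test.

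**3. Why separate verdicts disagree.** Two independent tests, each with power p, disagree with probability 2p(1 − p). At p = 0.805 this is 2 × 0.805 × 0.195 = 31%. Sharing the WL arm makes the verdicts positively correlated and lowers this somewhat.

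**4. Simulation with identical true indirect effects.** The sample size of 30 per arm and the shared WL arm come from the protocol. The path sizes are assumptions, because the protocol gives none: a = 0.5, 0.74 or 1.0 SD, equal for IE and IR; standardised b = 0.3, 0.4 or 0.5; direct effect 0.3 SD; no missing data; pre-treatment covariates left out. Each scenario used 1000 trials with 600 resamples and percentile intervals. Step 3 was simplified to a t-test.

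| a | b | step-4 verdicts disagree | step 3 rejects, all trials | step 3 rejects, discordant trials | interval for the difference excludes zero |
|---|---|---|---|---|---|
| 0.5 | 0.3 | 30.1% | 4.3% | 6.0% | 3.7% |
| 0.5 | 0.4 | 30.0% | 4.2% | 9.7% | 4.5% |
| 0.5 | 0.5 | 36.4% | 5.5% | 11.8% | 6.0% |
| 0.74 | 0.3 | 36.7% | 4.7% | 6.3% | 3.9% |
| 0.74 | 0.4 | 28.5% | 3.8% | 7.4% | 4.4% |
| 0.74 | 0.5 | 21.0% | 4.5% | 10.5% | 5.7% |
| 1.0 | 0.3 | 33.4% | 5.9% | 5.4% | 4.5% |
| 1.0 | 0.4 | 17.8% | 4.7% | 4.5% | 6.4% |
| 1.0 | 0.5 | 6.3% | 4.9% | 15.9% | 5.3% |

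The 15.9% rests on only about 63 discordant trials and is imprecise.

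**5. How often the steps conflict.** Multiply the disagreement rate by the share of those trials in which step 3 does not reject. For a = 0.74 and b = 0.4: 0.285 × (1 − 0.074) = 26%. The lowest is 0.063 × (1 − 0.159) = 5% and the highest 0.367 × (1 − 0.063) = 34%.

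**6. Cost of splitting the data.** The standard error of b scales roughly as 1/√n, so using 90 instead of 60 gives √(60/90) = 0.82. Simulation gave a ratio of 0.81, about 19% smaller. With one three-arm model, power for each indirect effect rose by up to about 18 points, with the smallest gains where b was already strong. Disagreement fell, though only slightly when a was weak. The interval for the difference wrongly excluded zero in about 4–7% of trials.

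**The case against.** The strongest reply is that the protocol already names its test for this question. Step 3 is introduced as the way to investigate whether the mechanisms differ, and it compares IE with IR directly. Step 4 has another job: to show whether a mediator carries the effect of each therapy against WL. If b is common, as the protocol argues, step 3 and a contrast of indirect effects test essentially the same hypothesis, and step 2 has already screened out mediators unrelated to outcome. Step 3's false-difference rate in the table is nominal, at about 4–6%.

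This stands, and it limits the point. A reader might infer that uniqueness will be read off the two step-4 verdicts, and so that the trial would wrongly label mediators as therapy-specific in 6–37% of cases. The document does not support that. It never says a discordant pair defines a unique mediator, and the 6–37% only counts how often the pair disagrees.

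What the reply leaves open is narrower. Step 4 abandons the common-path premise on which step 3 relies. Step 3's model may include a mediator-by-condition interaction, but no decision is tied to it, and variance explained is only inspected. No precedence is given when the steps disagree.

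The Discussion concedes that power may be too low to detect IE-versus-IR differences in mediators. That lowers the stakes, but it warns of missed differences and not of apparent ones.

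**Conclusion.** The point holds in a limited form. Step 4 offers no interval for the quantity that the first aim concerns, its handling of the mediator-to-outcome path is inconsistent with step 3's rationale, and the plan is silent on which step governs. With equal true indirect effects, discordant step-4 verdicts occur in roughly 6–37% of trials, and step 3 supports a difference in only about 5–16% of those. Conflict between the steps would therefore not be rare, except when both paths are strong.

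These figures depend on assumed path sizes and a simplified model without baseline covariates or missing data. The question is exploratory and its low power is acknowledged, so severity is modest: a cheap improvement.

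**What to change.** In step 4, fit one three-arm model per mediator, with indicators for IE and IR, WL as reference and a common mediator-to-outcome path. Check the mediator-by-condition interaction and report it. Bootstrap three quantities: the IE indirect effect, the IR indirect effect and their difference.

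Add a sentence that discordant verdicts against WL do not establish uniqueness, and that a mediator is called unique to one therapy only on the direct IE-versus-IR contrast. Otherwise report the two indirect effects as not distinguishable. Keep the separate IE + WL and IR + WL models as a sensitivity check.

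The cost is a change of model specification and wording, with no new participants, visits or data. The drawbacks are reliance on the common-path assumption, which the protocol already makes, and fewer claims of uniqueness.

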
## Discussion

With the proposed RCT, we aim to explore mechanisms of change in rescripting-based and exposure-based treatments for nightmare disorder. For this purpose, we introduce adapted IR and IE treatment protocols for nightmare disorder, each including one primarily active treatment component (i.e., either rescripting of, or exposure to, the nightmare content, respectively). Next to investigating the efficacy of these stripped-down treatments when compared to a waiting-list control condition, the research design of the proposed study enables us to explore proposed mediators of the treatment effect for IR and IE. Studying mediators can offer important knowledge about the underlying working mechanisms of psychological treatments, which might improve the effectiveness of everyday clinical practice.

The study has several methodological strengths. First, it follows the standard for evaluating the efficacy of psychological treatments (e.g., randomization of participants to three conditions, including a waiting-list control condition, allocation is concealed by means of randomization by independent staff members, post-assessment conducted by blinded researchers). Second, the current research design is well-suited to study mediators of change for the treatment effect of IR and/or IE for nightmare disorder, which might be a first step toward identifying possible mechanisms of change for these treatments [20]. More specifically, measuring several potential mediators simultaneously at multiple time points throughout the trial (i.e., preceding the intermediate treatment effect assessments) allows us to establish temporal as well as causal relationships between proposed mediators and therapeutic outcome measures [20, 21]. Another advantage of the proposed study is its use of stripped-down treatment formats. This method enables us to gather relevant information about the efficacy of specific treatment techniques (i.e., IR and IE) rather than nonspecific treatment components (e.g., nightmare journals, relaxation exercises, extensive psychoeducation about sleep and nightmares). Accordingly, the proposed trial does not aspire to design the most efficacious treatment package for nightmare disorder, but it rather aims to investigate the efficacy of the separate treatment components, and to explore differences and similarities in efficacy and working mechanisms between rescripting-based and exposure-based nightmare treatments. In order to draw conclusions about the active component of nightmare therapies, we find it important to study the two treatment techniques in isolation. Once we have examined the two techniques separately, future studies should concentrate on creating the optimal treatment package for nightmare disorder.

The proposed study also has a number of weaknesses. First, consistent mediator assessment might be compromised by the logistical complexity of the study. More specifically, while we aim at assessing treatment outcome variables and mediators every 7 days, appointments might sometimes be cancelled and/or rescheduled. In order to maintain the temporal relationship between mediators and outcome variable measurements as stable as possible, appointments may only be (re)scheduled to a *later* time point. Second, due to practical considerations, the proposed study has a relatively small sample size. Therefore, its statistical power might be too small to detect statistically significant differences between IE and IR with regard to treatment efficacy and/or mediators of change. However, exploring potential differences between IE and IR might inspire future research in this domain. Third, the waiting-list period of the proposed study is rather short. As a consequence, we cannot assess the long-term effects of the stripped-down treatments. However, if the results of the proposed trial support the efficacy of both interventions, future research might directly compare the two techniques as described in the present treatment protocol to a waiting-list condition with a longer waiting period. Fourth, two of the questionnaires used in the present study have not yet been validated (NDIQ and NBQ). It should be noted that the outcome variables used in nightmare treatment studies often lack precise definitions. With regard to nightmare research, it has become customary to assess nightmare frequency and nightmare distress. Such nightmare distress can be measured either in terms of distress directly associated with nightmares (e.g., NDQ [57]), or in terms of the effects nightmares have on a person’s life (e.g., NES [58]). While these questionnaires tap into different constructs of nightmare distress, they also show some considerable overlap. Therefore, we decided to create a nightmare distress outcome measure (i.e., NDIQ), which combines different aspects of nightmare distress in a single questionnaire. We acknowledge that a lack of validation might reduce confidence in the NDIQ as an outcome measure. However, the NDIQ is constructed from items resembling those of two validated questionnaires (NDQ and NES). Given that the items included in the NDIQ are very similar to those from these other questionnaires, we expect the NDIQ to be a valid and reliable measure. As to the NBQ, it should be mentioned that dysfunctional nightmare beliefs have not systematically been studied to date. The NBQ, a novel questionnaire altogether, aims to assess the occurrence of dysfunctional nightmare beliefs in nightmare sufferers. It was constructed to resemble other validated dysfunctional beliefs questionnaires (e.g., Dysfunctional Beliefs and Attitudes about Sleep [74]; Panic Belief Inventory [75]; Metacognitions Questionnaire [76]). To assess the psychometric properties of the NDIQ and NBQ, prior to data analyses, both questionnaires will be validated within a representative sample of nightmare sufferers and healthy controls. Fifth, the selected mediators are assumed to play a crucial role in IE, IR, or both. While we acknowledge that there are a multitude of (other) proposed theories and processes underlying IE and IR, we focus on those variables that have recently received much attention in the empirical literature and that seem especially relevant in the treatment of nightmares. Accordingly, it is possible that other relevant processes or variables were disregarded.

Taken together, the proposed project offers a unique opportunity to investigate the efficacy of two core treatment techniques for nightmares (IR and IE), and to explore and identify their mechanisms of change. More specifically, by including mediator and outcome variable assessments at multiple time points throughout the study, we intent to investigate temporal relationships between changes in mediators and their effects on outcome measures, which are needed to determine causal pathways of therapeutic change. Thus, with the proposed trial, we aim to provide new insights in the mechanisms of change of IR and IE for nightmares and thereby contribute to the improvement of such treatments. Moreover, given that rescripting as well as exposure techniques are also used in the treatment of other disorders, the results of the current study might provide useful knowledge about the working mechanism of these therapeutic techniques in general.

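### The article says the design can establish causal mediator-outcome relationships, but the step-4 mediation test cannot separate mediation from an unadjusted post-baseline common cause

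*Protocol article*

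**What the plan says.** In the Discussion paragraph on methodological strengths, the article says that assessing several mediators repeatedly, before the intermediate outcome assessments, "allows us to establish temporal as well as causal relationships between proposed mediators and therapeutic outcome measures". The sentence before it is more cautious and speaks of a possible first step towards mechanisms. The closing paragraph of the Discussion describes the temporal relationships as ones "which are needed to determine causal pathways of therapeutic change".

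The decisive analysis is step 4 in Statistical methods, Mediation. IE and IR are each compared with the waiting list. Change in the mediator predicts the post-assessment outcome, and "Pre-treatment levels of the dependent and mediator variables will be added to the model as covariates". Mediation is judged from the 95% bootstrap interval of the indirect effect, in single-mediator and multiple-mediator models. Covariates in the step-3 model are those that might reduce error; none is named as a confounder.

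The Sample size section concerns efficacy only. It uses a "medium to large effect size for individual nightmare therapy" (d = .74) and finds that "30 participants in each condition would suffice to detect a statistically significant difference". No figure is given for the mediation test. The Discussion lists five weaknesses. The closest one admits that relevant processes may have been left out, but none mentions confounding of the mediator-outcome path.

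**The concern.** Randomisation protects the comparison of treatment with waiting list on the mediator (path a) and on the outcome. It does not protect the association of mediator change with outcome within condition (path b). Measuring the mediator first rules out reverse order but not a shared cause, such as general improvement, mood or an unmeasured working process.

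The article's own measures make some residual correlation plausible:

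- Mediators and outcomes are self-reports from people who know whether they are being treated or waiting (Procedure).
- Each mediator rests on a single item (Table 2).
- The nightmare-distress mediator item asks about harm to daily functioning, and a sample item of the NDIQ, the second primary outcome, asks nearly the same thing.
- The Mediation section itself expects some mediators to be highly associated.

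Identifying mediators is the first aim under Trial objectives, and one planned paper is on mechanisms (Dissemination of results). A variable that treatment moves, but that does nothing to nightmares, could be published as a causal mechanism of IR or IE.

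**Working it through.** **Step 1: the article's own figure.** Inputs are "two-sided, power = 80 %, alpha = 0.05; G*Power 3.1" and d = .74. The normal approximation gives n = 2(1.960 + 0.842)² / 0.74² = 28.7, so 29 per arm. The exact noncentral t gives power 0.791 at 29 and 0.805 at 30. The stated 30 per condition is reproduced, so each step-4 comparison has 60 people.

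**Step 2: what step 4 estimates.** Write dM for mediator change, M0 and Y0 for the baselines, Y1 for the post-assessment outcome and X for condition.

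- Path a: coefficient of X in dM ~ X + M0 + Y0.
- Path b: coefficient of dM in Y1 ~ X + dM + M0 + Y0.
- Indirect effect: a × b.

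Suppose dM has no effect on Y1, but the residuals of the two correlate at ρ with equal SDs. Then b tends to ρ rather than 0, and a × b tends to a × ρ. With a = 0.74 and ρ = 0.3 this is 0.74 × 0.3 = 0.222; the simulated mean was 0.222. With a total effect of 0.74 as well, the apparent proportion mediated is 0.222 / 0.74 = 30%, although the truth is zero.

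**Step 3: how often the interval excludes zero.** Simulated with 30 v 30, true mediator effect zero and a percentile-bootstrap 95% interval. *Assumptions, not in the article:* ρ, and the size of a (0.74 is the article's efficacy benchmark and is not given for any mediator). The outcome is continuous. The rows differ in whether a is expressed in residual SDs or in total SDs with baseline-post correlation 0.5. In the second case 0.74 total SD equals 0.74 / √0.75 = 0.85 residual SD, which explains the higher rates. Ranges within a cell come from separate runs.

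| Effect on mediator | ρ = 0 | 0.1 | 0.2 | 0.3 | 0.5 |
|---|---|---|---|---|---|
| 0.5 residual SD | 2.4% | 5.8% | 12.0% | 25.4% | 47.7% |
| 0.5 total SD | 3% | 6% | 19% | 34% | 59% |
| 0.74 residual SD | 5.2% | 9.7% | 25.0% | 47.7% | 79.2% |
| 0.74 total SD | 5-6% | 9-11% | 25-31% | 54-57% | 87-89% |

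These runs used fewer resamples than the planned minimum of 5000. A check with 5000 (0.74 residual SD, ρ = 0.5, 200 trials) gave 76%, against 79.2%.

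**Step 4: what drives it.**

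- *Treatment moves only the mediator:* with no treatment effect on the outcome and a = 0.74, the rates are 46.8% at ρ = 0.3 and 78.5% at ρ = 0.5. An effect on the outcome is not needed.
- *Treatment does not move the mediator (a = 0):* the rate stays at or below 5.6% for ρ up to 0.7.
- *Stable shared trait captured by the baselines:* 3.6%, so no inflation.
- *Larger sample:* at 500 per arm and a = 0.74, the rates are 88.5% at ρ = 0.1 and 100% at ρ = 0.3. This is bias, which a larger trial would not cure.

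**The case against.** **The caveat is generic and the article is hedged.** Any analysis of a non-randomised mediator carries it, and elsewhere the article speaks of exploring possible mechanisms. That is fair on tone. But the sentence on causal relationships is unconditional, is listed as a strength, and is not withdrawn anywhere.

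**Step 4 does not stand alone.** Mediators are first screened by lagged prediction, highly associated ones may be combined, and multiple-mediator models are planned. This stands in part: those models help against confounding by the other measured mediators, and the baselines absorb a stable response style. Neither deals with an unmeasured cause acting after baseline, and a lagged association can come from the same cause. The simulation has one unscreened mediator, so its rates are illustrative.

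**The inputs are assumed.** This stands. At ρ = 0.3, an effect on the mediator of 0.3 SD gave 18%. Nightmare frequency, the first primary outcome, is a count and was not simulated.

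**A sensitivity analysis can be left to an analysis plan.** Agreed. Its absence here is not the finding; the stated causal claim is.

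A reader might infer more than the article supports:

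- *That the test fails whenever any other shared cause exists.* Rejection is a probability: 6-11% at ρ = 0.1 in these runs, and not inflated when the baselines capture the cause.
- *That the article tests a stated null of no causal effect of the mediator.* It states no such null; it evaluates the interval of the indirect effect.
- *That the closing paragraph repeats the causal claim.* It calls temporal relationships needed for determining causal pathways, which is a necessary condition and not a claim of sufficiency.

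**Conclusion.** The point holds in a limited form. The article credits the design with a property that neither the design nor the step-4 test has: repeated measurement and randomised treatment do not by themselves establish a causal effect of a mediator on outcome. When treatment moves the mediator and a moderate or strong unadjusted post-baseline cause is present, the false-positive rate is well above 5%. For an effect on the mediator of 0.5 to 0.74 SD it is about 25-57% at residual correlation 0.3 and 48-89% at 0.5. At 0.1 the excess is small. These sizes depend on assumed correlations, an assumed effect on the mediator and a continuous outcome; the direction of the problem does not. What can be concluded about mechanisms changes. The efficacy comparisons with the waiting list do not.

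**What to change.** 1. In the strengths paragraph of the Discussion, replace the claim of temporal and causal relationships with *temporal associations consistent with mediation*. The closing paragraph needs at most matching wording.
2. In the weaknesses paragraph, state that the mediation analysis assumes no unmeasured mediator-outcome confounding, and that the design cannot verify this.
3. With each step-4 indirect effect, report the residual mediator-outcome correlation at which the estimate becomes zero and the one at which its interval first includes zero. In the linear model the first is simply the observed partial correlation of mediator change with outcome, given condition and both baselines. For nightmare counts, state the scale on which the correlation is defined.
4. Set no pass/fail threshold. Requiring the interval to withstand a correlation of 0.3 would discard real mediators at this size. With a = 0.74 and no confounding, detection of a true mediator with partial correlation 0.4 falls from about 82% to 13%, and with 0.5 from 88% to 42%.

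The cost is a weaker stated claim and a small amount of analysis on data already planned. No extra participants or assessments are needed.
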